**Secondary outcome B:**
*Timeliness.* Difference in timeliness of MVs administered, measured as median age of vaccinated children.

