**Secondary outcome C:**
*Average number of visits* to the health center (with the purpose of receiving MV) needed before MV is successfully administered.

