#### Sample Size Calculations

Current statistics indicate MV coverage of approximately 75% at 12 months of age in the rural areas of Guinea-Bissau. Drawing on experiences from other studies implementing SMS reminders [13], we aim for an increase in MV coverage of 10 percentage points. Using a significance level of 5% and 80% power, and a hypothesized increased MV coverage to at least 85% in each of the intervention arms (compared to the control arm), a total of 810 children are needed (270 in each arm). Adjusting for expected loss-to-follow-up between 15-20% (eg, outmigration, death, children being vaccinated elsewhere), which is comparable to other mHealth studies [27], we plan to enroll 990 study participants (330 in each arm).

The current median age of MVs given before 12 months of age in rural Guinea-Bissau is approximately 295 days of age [7]. The age distribution is fairly normal, and in the following power calculation we have used a normal approximation: with 270 children in each arm and an MV coverage of at least 75%, we are able to detect a change of 7 days in median age (using a significance level of 5% and 80% power).

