#### Statistical Analysis

The main outcome of MV coverage at 12 months of age (366 days of age) will be calculated as percent who received MV at the health centers, among all children enrolled. Furthermore, coverage will also be calculated based on follow-up interviews when children reach 13 months of age, among study participants whose children did not receive the MV at the health centers. The coverage (percentages) will be compared using Mantel-Haenszel statistics stratified for health center for each of the intervention groups (SMS and voice calls) compared with the control group. The secondary outcome B (Textbox 1) of timeliness of MVs will compare age distributions between vaccinated children, among all children having received MVs before 12 months of age (366 days), using linear regression adjusted for health center. A statistical significance level of 5% will be used. A subanalysis will stratify for study participants having their own private mobile phone versus those using the phone number of another community member. Due to the groups being randomized, we do not expect baseline imbalances. In the case that such trends do occur, we will be unable to rule out other imbalances or unmeasured confounders. The main outcome will therefore be the crude estimate. However, we will investigate the impact of adjusting for unbalanced background factors in sensitivity analyses. The study will be conducted and reported in accordance with Consolidated Standards of Reporting Trials guidelines [28].

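### Timeliness is compared only among vaccinated children, a group the intervention itself is meant to enlarge, so a real speed-up can be diluted and the comparison is no longer randomized

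*Protocol article*

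**What the plan says.** Textbox 1 of the protocol article defines secondary outcome B as "Difference in timeliness of MVs administered, measured as median age of vaccinated children". The Statistical Analysis section fixes both population and method: ages are compared "among all children having received MVs before 12 months of age (366 days), using linear regression adjusted for health center". The Sample Size Calculations section gives the timeliness power for 270 children per arm and coverage of at least 75%: "we are able to detect a change of 7 days in median age", at 5% significance and 80% power.

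On coverage, the same section says "Current statistics indicate MV coverage of approximately 75% at 12 months of age" and plans for a "hypothesized increased MV coverage to at least 85% in each of the intervention arms". The primary outcome is coverage by 366 days among all enrolled children. The Intervention section sends a fresh set of reminders at each further vaccination opportunity while the child is unvaccinated and between 9 and 12 months old. No analysis of age at vaccination in all randomized children is described.

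**The concern.** Being vaccinated by 366 days is both the primary outcome and the entry condition for the timeliness analysis. At the planned effect, about 10 of every 85 vaccinated children in an intervention arm would have gone unvaccinated under control. Their control counterparts are left out of the age comparison. The two vaccinated groups are therefore different kinds of children, and randomization does not protect the comparison.

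A child who is vaccinated only after several reminders enters the intervention mean at a late age. If that is typical, success on coverage pulls the intervention mean upward and hides a real speed-up. The Objectives section names timeliness alongside coverage, so a misleading null or an apparent delay would matter to how the programme is judged.

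**Working it through.** **1. The plan's own figures.** For 75% against 85%, two-sided 5% and 80% power, the standard formula gives 250 per arm without continuity correction and 270 with it, which matches the plan. Sidedness is not stated; two-sided is assumed.

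The 7-day figure cannot be reproduced directly because no standard deviation is given. Solving backwards with 0.75 × 270 = 202.5 vaccinated children per arm: SD = 7 / [(1.960 + 0.842) × √(2/202.5)] = 25.1 days.

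**2. Expected difference.** Inputs from the protocol: coverage 75% and 85%, and a current median age of 295 days, used as the mean because the protocol calls the distribution fairly normal. Inputs assumed: a speed-up of d days in children who would be vaccinated anyway, and a mean age m for the children gained. Then

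observed mean difference = [75 × (295 − d) + 10 × m] / 85 − 295.

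For d = 7, 75 × 288 = 21,600. The power column gives simulated power of the vaccinated-only comparison:

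| m (days) | Calculation | Difference (days) | Power |
|---|---|---|---|
| 288 | (21,600 + 2,880)/85 − 295 | −7.0 | 85% |
| 295 | (21,600 + 2,950)/85 − 295 | −6.2 | not simulated |
| 305 | (21,600 + 3,050)/85 − 295 | −5.0 | not simulated |
| 320 | (21,600 + 3,200)/85 − 295 | −3.2 | 25% |
| 340 | (21,600 + 3,400)/85 − 295 | −0.9 | 6% |
| 350 | (21,600 + 3,500)/85 − 295 | +0.3 | 5% |

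With a 7-day speed-up and no coverage gain, simulated power is 81%, in line with the plan. The simulation used 3,000 runs, 270 children per arm, ages normal with SD 25.1 in children vaccinated anyway and SD 8 in gained children, ages capped at 366 days, and an unadjusted two-group comparison of means.

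**3. No speed-up (d = 0).** The difference is 10 × (m − 295)/85: +2.9 days at m = 320 and +5.3 at m = 340. At 340 this false delay was significant in 56% of simulated runs.

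**4. Reversal of sign.** The difference is zero when 75d = 10(m − 295), that is m = 295 + 7.5d. This gives 317.5 days for d = 3, 332.5 for d = 5 and 347.5 for d = 7. Since m cannot exceed 366, reversal in expectation is impossible once d exceeds (366 − 295)/7.5 ≈ 9.5 days. If coverage rises by only 5 points, the break-even for d = 7 is 295 + 15 × 7 = 400 days, which cannot occur.

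**5. Median instead of mean.** Among vaccinated children with d = 7 and m = 340, the simulated median difference is −2.8 days. The bias is smaller but still present.

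**6. All randomized children.** With unvaccinated children held to 366 days and d = 7, simulated log-rank power is 86% at m = 320 and 75% at m = 340. With a 7-day speed-up and no coverage gain it is 18%, against 81% for the planned analysis.

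**The case against.** The strongest reply is that the size depends on m, which no passage gives. The first reminders go out when the child becomes eligible, so gained children may come early. At 288 to 305 days the dilution runs from nothing to 2 days. This stands: the loss of power is a scenario, while the conditioning on a post-randomization event is stated in the text whatever m is.

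A reader might infer more than the documents support:

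- **That the plan would reverse a real speed-up.** For 7 days this needs gained children to average more than 347.5 days. Otherwise it needs a smaller speed-up. Dilution is the more general result.
- **That the 7-day power statement is simply wrong.** It concerns a 7-day difference among vaccinated children and is consistent with an SD of about 25 days. It fails as a statement about speed only if the intervention changes which children are vaccinated.
- **That median against mean is a serious fault.** Under the stated near-normality the two nearly coincide. It is a wording mismatch to reconcile.
- **That outcome C needs the same change.** It is defined as visits "needed before MV is successfully administered", and the protocol describes no recording of visits for children who are never vaccinated, so an all-children version lacks a stated data source.

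It is also fair to say that an all-children analysis answers a different question, since it combines speed with coverage.

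**Conclusion.** The point holds. As written, the timeliness comparison conditions on an outcome the intervention is designed to change, so it cannot be read as a randomized effect on speed. At the plan's 75% and 85%, a true 7-day speed-up would appear as anything from about 6 days to about 1 day as the mean age of gained children goes from 295 to 340 days, with power about 25% at 320 days and about 6% at 340. These sizes rest on the assumed age of gained children, an SD back-solved from the plan, and 295 days taken as a mean.

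This should be fixed, but it does not threaten the trial's main result: Textbox 1 makes timeliness a secondary outcome, and primary coverage is calculated among all enrolled children. Reporting coverage alongside helps interpretation but does not correct the timeliness estimate.

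**What to change.** - **Main analysis.** Analyze age at vaccination in all randomized children from the center-recorded dates. Treat children not recorded as vaccinated as unvaccinated at 366 days, and censor earlier only where a date of death or migration is known. Suitable forms are Kaplan-Meier curves with a center-stratified log-rank or Cox analysis, or coverage at 10 and 11 months with the all-children median age (estimable, as expected coverage exceeds 50% in every arm).
- **Supportive analysis.** Keep the vaccinated-only regression, labelled descriptive.
- **Wording.** Align the median in Textbox 1 and the sample size section with the mean-based regression, and qualify the 7-day power statement as holding only if the intervention does not change which children are vaccinated.

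For center vaccinations this is a change of analysis text, because the Follow-Up section already records the date. Dates of vaccination elsewhere, death or migration are not clearly collected: the 13-month interview registers whether these happened, and no date is mentioned. Relying on them would need added data collection. The statistical cost is the loss of power when only speed changes (18% against 81%), so the plan should say openly that the new analysis measures speed and coverage together.

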## Discussion

### Possible Constraints

External threats to the project, such as strikes in the health sector, shortages of measles vaccine, and other interventions in the same region, will prompt ad-hoc decisions. Problems with vaccine delivery to the vaccination sites will result in the rescheduling of intervention messages (eg, the reminder messages can be rescheduled until vaccine is restocked).

### Dissemination of Results and Publication Policy

Articles are planned for each of the main study components. The main article, concerning the second study component, will contain a statistical analysis linking the effect the mHealth intervention to health outcomes in terms of MV coverage and timeliness. The primary author of the article will be [name], with the remaining core members of the project team listed as contributing authors.

A second article will analyze the cost and effect of the mHealth intervention, linking the intervention to vaccination coverage, and add to the evidence base for mHealth interventions. In addition to these articles, the findings of this study will be presented to the National Ministry of Health in Guinea-Bissau, which will also be included as much as possible during the project implementation.

### Limitations and Anticipated Problems

Several problems are anticipated in this study, including technical obstacles such as an unstable cellphone network, and low or no signal in some areas. In order to mitigate these issues, extra attention will be given to *delivery reports* to ensure that the text messages are delivered correctly. In addition, the impact of network-related problems will be covered by the follow-up questionnaire.

The project is also vulnerable to other interventions related to the MVs that are being carried out within the study area, since this could distort the findings of this study. To minimize this risk, the study team will coordinate closely with the National Ministry of Health in Guinea-Bissau.

By only enrolling participants who have access to mobile telephones, there is a risk of potentially adding to social injustice by focusing on a selected demographic with comparably better access to resources, sometimes referred to as *digital divide*. However, we have tried to mitigate this problem by defining *access to a mobile telephone* in the broadest sense possible, by also including participants who will receive the reminder message on the phone of their community’s *health communication agent*. Such agents will be community residents employed by the Ministry of Health as contact points to disseminate information about health events, such as vaccination campaigns. These agents will also help to mitigate the limitation of study participants that do not speak Creole. However, the fact that there are multiple spoken languages in the study area still poses a limitation to the project.

## Abbreviations

GAVI: Global Alliance for Vaccines and Immunization
INDEPTH: International Network for the Demographic Evaluation of Populations and Their Health
IT: information technology
mHealth: mobile health
MV: measles vaccination
RCT: randomized controlled trial
SMS: short message service
UNICEF: United Nations International Children's Emergency Fund
